**Figure 1 F1:**
[figure not shown]
Age-adjusted ten-year mortality rates for breast cancer by county among women in Michigan under age 50, 2000–2009.

As shown in Figure 2, it is estimated that from the initial 3,000 YBCS, approximately 1,200 will be willing to participate (40% response rate). We estimate that approximately 20% of these YBCS (n = 240) will not have any eligible high-risk female relatives (e.g. relatives will be younger than 25 or older than 64). These YBCS will be included in the study but will be analyzed as a separate group. Based on our previous experience recruiting women with familial breast cancer and their high-risk relatives [11], we project that the remaining 960 YBCS will have approximately 1,728 eligible high-risk female relatives. This estimation is based on the assumption that we will be able to identify 1.8 first- and/or second-degree, high-risk relatives per YBCS. Based on our previous experience [11], we expect that 604 high-risk relatives will be willing to participate in the study (35% response rate). Table 1 describes inclusion and exclusion criteria for YBCS and high-risk female relatives.

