6) Based on information provided by the YBCS in the baseline survey, the genetic counselors will identify up to two high-risk relatives per YBCS. Eligible high-risk relatives will be female, first- and/or second-degree relatives, and unaffected by cancer. Identification of high-risk relatives will be according to a protocol that involves pedigree analysis. Questions that assess family history of cancer allow calculations of Gail [12] and Claus [13] risk models. YBCS will be asked how many first and second degree relatives had cancer, type of cancer, and age of onset. Then YBCS are asked to list the first and second degree relatives in the family who are cancer free, their age, and whether they are willing to contact them for the study. The combination of answers in these two sets of questions allows genetic counselors to identify eligible, high-risk relatives. As explained in the informed consent form, if necessary, the genetic counselors will contact the YBCS by phone to obtain additional family history information. Each participating YBCS will be mailed a letter asking her to contact the identified high-risk relatives and request their participation in the study. Consent forms, baseline surveys and postage-paid return envelopes will be provided to the YBCS to give to her relatives. A “Project Navigator” will be available by telephone to discuss any concerns the YBCS may have about this procedure. If an identified high-risk relative does not mail back her signed consent form and completed baseline survey within six to eight weeks, the Project Navigator will contact the YBCS to determine if an alternate high-risk relative should be selected for participation.

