### Stratification and randomization

Before randomization, YBCS (with and without high-risk relatives) will be stratified by self-reported race (black vs. other) to ensure equal distribution of ethnic minority participants across study arms. YBCS (n = 960 with high-risk relatives and n = 240 without high-risk relatives) will be randomly allocated to receive either the Targeted or the Enhanced Tailored version of the intervention via a computerized program generated by the study statistician. YBCS and high-risk relatives will be randomly assigned as a family unit.

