### Sample size (power analysis)

Data analyses to meet Aim 3 will require comparison of randomly assigned subsamples of the entire sample and make the most demand on the sample size. PASS software [28] was used to determine the number of participants needed to provide 80% power to detect a medium-small difference (d = 0.3) between means or between percentages (h = 0.3) using a two-tailed test with alpha of 0.05. A medium-small effect size (d = 0.3 or h = 0.3) is a typical effect size found in interventions aiming to increase screening mammography [17,18]. The result of power analysis was 176 participants per group or 352 in total. Assuming 35% attrition between baseline and follow up, 542 participants must be given the intervention to maintain this level of power. Given the initial target number for recruitment and the expected response and attrition rates, the study will recruit and maintain a large enough sample size to perform data analyses for Aim 3 (see Figure 3).

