### Statistical analyses

Analyses will be conducted separately for YBCS and high-risk relatives. A descriptive analysis of baseline data will provide screening utilization practices, perceived barriers and facilitators to screening, and other outcomes for YBCS and high-risk relatives. This will include tabulating counts and frequencies of variables including demographics, cancer history, screening history and perceived breast cancer risk. Bivariate analyses (using the Chi-square test for differences in proportions and *T*-test for differences in means) to assess the associations between demographic factors, clinical indications and screening practices will follow. We will stratify by using the Cochran-Mantel-Haenszel test to assess the association between family history, screening practices, genetic counseling/testing, and perceived facilitators/barriers while controlling separately for race/ethnicity, age-group, and time since diagnosis. Outcomes include both continuous and dichotomous measures. Means and standard deviations will be used to describe the results. Continuous measures taken only at post-test will be compared between the two intervention groups by simple t-tests. After assuming an autocorrelation of data r = .30, changes over time in continuous measures will be tested by paired t-tests. For dichotomous measures taken only at post-test, the rates in the two groups will be compared by logistic regression. The proportions in each group will be reported to describe the results. If a baseline version of the measure is available, logistic regression will be conducted on the post-tests with the pre-tests included as covariates. Chi-square tests will be conducted to test the changes over time. The above analyses will establish whether the groups are equivalent, determine whether post-tests differ between the two groups, and assess the significance of changes over time. To further meet Aim 3, regression analyses (linear or logistic) will be used to test which factors (beyond the intervention) predict obtaining breast cancer screening.

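### Relatives are randomised by family, up to two per family, but their between-arm tests and the 352/542 sample size treat them as independent women; 80% power is not assured

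*Protocol article*

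**What the plan says.** All references are to the protocol article.

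- **Unit of randomisation** (Stratification and randomization): "YBCS and high-risk relatives will be randomly assigned as a family unit".
- **Relatives per family** (Recruitment of YBCS and high-risk relatives, step 6): "the genetic counselors will identify up to two high-risk relatives per YBCS". The same section assumes that "we will be able to identify 1.8 first- and/or second-degree, high-risk relatives per YBCS", which gives 1,728 eligible relatives from 960 survivors, of whom 604 (35%) are expected to take part.
- **Sample size** (Sample size (power analysis)): the target is "80% power to detect a medium-small difference (d = 0.3) between means", or "between percentages (h = 0.3) using a two-tailed test with alpha of 0.05". "The result of power analysis was 176 participants per group or 352 in total". Allowing for 35% attrition, this becomes 542. No ICC or design effect appears.
- **Analysis** (Statistical analyses): survivors and relatives are analysed separately. "Continuous measures taken only at post-test will be compared between the two intervention groups by simple t-tests". Dichotomous measures are compared by logistic regression, with the pre-test as covariate where one exists. No family term, mixed model, GEE or robust variance is mentioned. The one correlation given, r = .30, is between time points and not within families.

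**The concern.** Two relatives of the same survivor are always in the same arm. They share a family history and are approached by the same woman, and the Enhanced Tailored version works partly through family support. Their outcomes are therefore likely to be positively correlated. A t-test or a standard logistic regression counts them as two independent observations.

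Analysing survivors and relatives separately removes the survivor-relative correlation but leaves the relative-relative correlation in place.

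At stake is the relatives' part of Aim 3. Confidence intervals would be too narrow, the nominal 5% test would reject too often, and the effective sample size would be below the number counted. A larger sample would restore power but would not correct the standard errors.

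**Working it through.** **1. The plan's own figure.** Two-sample t-test, d = 0.3, two-sided alpha 0.05, independent women: 175 per group gives 79.9% power and 176 gives 80.1%. Then 352 / 0.65 = 541.5, so 542. Both stated figures reproduce, with a design effect of 1.

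**2. Projected completers.** 960 × 1.8 = 1,728; × 0.35 = 604.8 (stated as 604); 604 × 0.65 = 393. This is 12% above 352. With independent women, 393 completers give 84% power.

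**3. How many relatives are in pairs.** A mean of 1.8 with a maximum of two means that 768 families have two eligible relatives and 192 have one (2 × 768 + 192 = 1,728). The document does not say how many pairs take part, so I assume three cases for the share x of analysed relatives whose co-relative is also analysed:

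- Women respond and drop out independently: x = (1,536 / 1,728) × 0.35 × 0.65 = 0.20.
- Families respond all-or-none, dropout is independent: x = (1,536 / 1,728) × 0.65 = 0.58.
- Families respond and drop out together: x = 1,536 / 1,728 = 0.89.

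**4. Formulas.** With clusters of one or two:

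- design effect DE = 1 + x × ICC
- understatement of the naive standard error = 1 − 1/√DE
- type I error of the naive test ≈ 2(1 − Φ(1.96/√DE))
- power of a correctly sized test = two-sample t power at N / DE
- enrolment needed = 352 × DE / 0.65

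**5. Results.** The ICC is assumed, because the document gives none.

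| x | ICC | DE | SE too small by | Type I error | Power, 352 | Power, 393 | Enrol instead of 542 |
|---|---|---|---|---|---|---|---|
| 0.20 | 0.1 | 1.02 | 1.0% | 5.2% | 79% | 84% | 553 |
| 0.20 | 0.2 | 1.04 | 2.0% | 5.5% | 79% | 83% | 564 |
| 0.20 | 0.5 | 1.10 | 4.7% | 6.2% | 76% | 81% | 597 |
| 0.58 | 0.1 | 1.06 | 2.8% | 5.7% | 78% | 82% | 573 |
| 0.58 | 0.2 | 1.12 | 5.3% | 6.4% | 76% | 80% | 605 |
| 0.58 | 0.5 | 1.29 | 11.9% | 8.4% | 69% | 74% | 698 |
| 0.89 | 0.1 | 1.09 | 4.2% | 6.0% | 77% | 81% | 590 |
| 0.89 | 0.2 | 1.18 | 7.9% | 7.1% | 73% | 78% | 638 |
| 0.89 | 0.5 | 1.44 | 16.8% | 10.3% | 65% | 69% | 783 |

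**6. Break-even ICC at 393 completers.** (393/352 − 1) / x gives about 0.57, 0.20 and 0.13 for the three cases. Below these values the projected sample still has 80% power.

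**7. The Aim 3 exclusion.** Recruitment step 5 removes about 100 survivors with hereditary syndromes from Aim 3, and the 604 is not reduced for them. If their relatives also leave, in proportion, 1,100 × 0.8 × 1.8 × 0.35 = 554 enrol and 360 complete; the break-even ICCs fall to about 0.12, 0.04 and 0.03. If all 100 come from the 960, 860 × 1.8 × 0.35 = 542 enrol and 352 complete, which leaves no margin.

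**The case against.** **Power may survive.** The plan needs 352 completers and projects 393. At an ICC of 0.1 that margin keeps power at 81% to 84% in all three pairing cases, and at 0.2 it gives 78% to 83%. This stands. A reader might infer that the stated 80% is lost; the documents do not support that, because they give neither an ICC nor a pair count.

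**The upper figures are a worst case.** A 10.3% type I error or 65% power needs an ICC of 0.5 and relatives who both respond and drop out together. Relatives may be first- or second-degree and aged 25 to 64, so a high ICC is not established. This also stands: those figures bound the problem and do not describe the expected case. The option in step 6 of replacing a non-responding relative with an alternate does, however, point away from the mildest case.

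**The Aim 3 exclusion.** A reader might take 360 completers as the plan's true number. The text excludes the survivors; it does not say that their relatives leave. The smaller number is therefore conditional.

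**The quoted t-test covers little.** It applies to measures taken only at follow-up, and in Table 2 that is only the acceptability of the intervention. Screening use has a baseline and gets covariate-adjusted logistic regression. That is correct, but the logistic model is also named without a family term, so the problem reaches the key outcome.

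**An article condenses.** The variance estimator for the logistic model could be set out elsewhere. But a simple t-test is a named method that assumes independence, and the sample size rests on the same assumption. This is a stated choice and not an omitted detail.

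**Conclusion.** The point holds for relatives. Randomisation is by family, while the named tests and the 352/542 calculation treat relatives as independent. If any pairs are analysed and their outcomes are positively correlated, the standard errors are too small. Because 352 completers give only 80.1% power to begin with, all but a trivial design effect takes that number below 80%.

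The size is uncertain. Over an assumed ICC of 0.1 to 0.5 and 20% to 89% of analysed relatives in pairs, it runs from slight (design effect 1.02, type I error 5.2%) to material (1.44 and 10.3%). At the projected 393 completers, power is about 69% to 84%, and the margin shrinks further if relatives of the excluded survivors also leave. The supported conclusion is that 80% is not assured.

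The point does not extend to the survivor comparisons: there is one survivor per family and survivors are analysed separately.

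**What to change.** 1. **Statistical analyses:** for every between-arm test in relatives, replace the simple t-test and the logistic regression without a family term by a linear or logistic model that accounts for family. GEE with robust standard errors, a family random effect or cluster-robust standard errors would each serve. Include the baseline value as covariate where one exists.
2. **Sample size (power analysis):** restate the relatives' power with a design effect over an ICC range such as 0.1 to 0.5, with the assumed share of relatives in pairs. State whether relatives of the survivors excluded from Aim 3 remain in the count.
3. Leave the survivor between-arm analyses as they are.

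The cost is a change of wording and a slightly less favourable power figure for relatives. The analysis change needs no extra participants or data, only a family identifier in the relatives' data set.

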Aim 1: Identify and survey 3,000 female YBCS reported to the cancer registry who were diagnosed between the ages of 20–45 years and determine: (a) their current breast cancer screening status; (b) perceived barriers and facilitators to screening; (c) willingness to participate in an intervention to increase breast cancer screening; and (d) willingness to serve as a breast cancer screening advocate for their high-risk relatives.

Aim 2: Identify and survey up to two unaffected first- and/or second-degree female relatives per YBCS and determine: (a) their current breast cancer screening status; (b) perceived barriers and facilitators to screening; and (c) willingness to participate in an intervention to increase breast cancer screening. Female relatives will be between 25–64 years and have an increased risk of breast cancer based on the YBCS’ age of diagnosis.

Aim 3: Compare the efficacy of two versions of an intervention on breast cancer screening utilization and other outcomes among YBCS and their high-risk female relatives. YBCS and their high-risk female relatives will be randomly assigned as a family unit to receive either the Targeted or the Enhanced Tailored version of the intervention. (Description of the two intervention methods follows).

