### Outcomes

A follow-up survey will be mailed to YBCS and their high-risk relatives nine months after the baseline survey to determine the effect of each intervention version on: a) utilization of breast cancer screening and genetic counseling; b) perceived barriers and facilitators to screening; c) self-efficacy in utilizing screening services; d) family support related to screening; e) knowledge of the genetics of breast cancer; and f) satisfaction with the intervention. Table 2 describes the concepts and variables of the study (left column), the instruments that will be used to measure these variables (middle column), and the assessment times (right column). Instruments have been previously validated with various populations (see references in Table 2). Completion of the baseline and the follow-up questionnaires takes approximately 45 min.

**Table 2 T2:** Variables, instruments and assessment times

**Concepts/variables**	**Instruments**	**Survivor**		**High-risk relative**	
		**Baseline**	**Follow up**	**Baseline**	**Follow up**

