**Knowledge/Attitude**					
Perceived breast cancer risk	Perceived breast cancer risk [11,20]			√	√
Knowledge of breast cancer risk factors	Breast cancer risk factor knowledge index [11,21]	√	√	√	√
Knowledge of breast cancer genetics	Knowledge of breast cancer gene inheritance [22]	√	√	√	√
Perceived facilitators vs. barriers of mammography screening	Decisional balance scale for mammography [23,24]	√	√	√	√

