**Family support**					
Perceived family support for breast cancer screening	Social support for breast cancer screening [25]	√	√	√	√

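### For continuous measures taken at both surveys, the plan names a paired t-test of change but no test that compares Targeted with Enhanced Tailored

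*Protocol article*

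**What the plan says.** Aim 3 in the Background of the protocol article is to "Compare the efficacy of two versions of an intervention on breast cancer screening utilization and other outcomes among YBCS and their high-risk female relatives". Besides utilization, the Outcomes section lists five domains: barriers and facilitators, self-efficacy, family support, genetics knowledge, and satisfaction.

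The Statistical analyses section assigns methods by type of measure:

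- Continuous, collected at follow-up only: two-sample t-test between arms.
- Continuous, change over time: "After assuming an autocorrelation of data r = .30, changes over time in continuous measures will be tested by paired t-tests".
- Dichotomous, collected at follow-up only: logistic regression between arms.
- Dichotomous with a baseline value: "If a baseline version of the measure is available, logistic regression will be conducted on the post-tests with the pre-tests included as covariates", with chi-square tests for change over time.

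The section then says that these analyses will show whether the arms differ at follow-up and whether changes over time are significant. It closes with linear or logistic regression to find which factors other than the intervention predict screening.

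**The concern.** The between-arm t-test is confined to continuous measures that have no baseline value, and baseline adjustment is given only to logistic models. A continuous scale collected at both surveys falls between the two. Its one named test is within-person, so it cannot show which version of the intervention did better.

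The section therefore promises a between-arm result at follow-up that its listed methods do not deliver for these scales. Whoever analyses the data would have to choose a between-arm method later. The candidates (follow-up score alone, change score, baseline-adjusted score) differ in power and can give different answers, so the choice should be fixed before outcomes are compared by arm.

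The sentence also attaches an assumed correlation to a test that does not take one.

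**Working it through.** **1. Which outcomes fall in the gap.** Each outcome domain in the Outcomes section is set against its timing in Table 2 and the methods in Statistical analyses.

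| Outcome domain | Table 2 timing | Between-arm method named |
|---|---|---|
| Screening and genetic counseling use | current screening practices: both surveys | yes, logistic with pre-test, if dichotomous |
| Barriers and facilitators ("Decisional balance scale for mammography") | both surveys | none, if continuous |
| Self-efficacy | both surveys | none, if continuous |
| Family support ("Perceived family support for breast cancer screening") | both surveys | none, if continuous |
| Knowledge ("Knowledge of breast cancer genetics") | both surveys | none, if continuous |
| Satisfaction/acceptability | follow-up only | yes, t-test or logistic |

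Four of the five domains other than utilization are affected. Subjective norms and intention are also collected at both surveys in Table 2, but the Outcomes section does not list them, so they are not counted here.

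**2. The plan's own sample size.** Inputs from the Sample size section: d = 0.3 (or h = 0.3), two-sided alpha 0.05, power 80%, attrition 35%.

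- Normal formula: n per arm = 2 × (1.96 + 0.8416)² / 0.3² = 174.4, rounded up to 175.
- Exact two-sample t-test: 175.4, rounded up to 176. This matches the stated 176 per group (352 in total).
- Attrition: 352 / (1 − 0.35) = 541.5, rounded up to 542, as stated.

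The trial is thus sized for an independent two-arm comparison and not for a paired test.

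**3. Power of the candidate between-arm analyses at 176 per arm.** Take d = 0.3 in units of the raw SD, and read the plan's r = .30 as the correlation between baseline and follow-up. Power ≈ Φ(0.3 × √(176/2) / k − 1.96), where k is the SD factor of the analysis and 0.3 × √88 = 2.814.

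| Analysis | k | 2.814/k | Power at 176 | n per arm for 80% (174.4 × k²) |
|---|---|---|---|---|
| Follow-up score only | 1 | 2.814 | 80.4% | 175 |
| Baseline-adjusted regression | √(1 − 0.30²) = 0.954 | 2.950 | 83.9% | 159 |
| Change score | √(2 × (1 − 0.30)) = 1.183 | 2.378 | 66.2% | 245 |

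The baseline-adjusted model fits within the planned sample. The spread from 66% to 84% shows that leaving the method open matters.

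**4. The assumed r.** A paired t-test divides the mean within-woman difference by the standard error of the observed differences. The correlation is already contained in those differences, so an assumed value has no place in the test. It could serve as a planning value for power, as in step 3.

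**The case against.** Several points on the other side stand.

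- The intention to compare arms is there. The section states it, and the sample size is built on a difference between two means. What is missing is a method, not an aim. The paired t-test can fairly be read as serving only the separate purpose of describing change over time, as the chi-square tests do for dichotomous measures.
- The article does not say which instruments are scored as continuous. Treating the four domains as continuous is an assumption, although a natural one for scales.
- Screening, which Aim 3 names first, has a baseline-adjusted between-arm model if it is dichotomous.
- An article condenses a fuller plan, and a linear counterpart to the logistic model may exist there. This does not remove the point. The article does not leave the method open: it confines the between-arm t-test to measures without a baseline and names only a within-person test for change in the others. The closing linear or logistic regression does not fill the gap either, because it concerns predictors of screening other than the intervention.

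Two stronger readings are tempting, and the document supports neither.

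- A reader might infer that the versions will be judged by whether change is significant in one arm and not in the other. With equal true change in both arms and power p for each within-arm test, exactly one arm is significant with probability 2p(1 − p): 50% at p = .5 and 32% at p = .8. These figures illustrate why such a rule would be unsafe. The plan does not state that rule, nor that the paired tests are run by arm.
- A reader might infer that r = .30 will replace the observed correlation in the standard error. With equal SDs at the two surveys, the ratio of imposed to true SE would be √((2 − 0.6)/(2 − 2r)): 1.32 if the true r is .6 (32% too large) and 0.88 if it is .1 (12% too small). The plan does not say that r will be imposed, and it gives neither of these true values.

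**Conclusion.** The point holds as a missing between-arm method that leaves the Statistical analyses section at odds with its own stated purpose. For continuous measures with a baseline value, the named test does not answer Aim 3. Four of the five outcome domains other than utilization are affected, provided that their scales are scored as continuous. Dichotomous screening and genetic counseling use, and satisfaction, are not affected.

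The gain in power from baseline adjustment is modest at the plan's own r = .30: about 84% against 80% for follow-up scores alone. Those figures assume d = 0.3, independent women and 176 per arm with follow-up data. The main gain is that the arm difference is estimated at all, by a method fixed in advance. The document does not support a finding that wrong conclusions or wrong standard errors are planned.

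**What to change.** In Statistical analyses, add one sentence: for each continuous outcome with a baseline value, the follow-up score will be analysed by linear regression on arm, baseline score and the race stratum used in randomization (black vs. other), and the adjusted arm difference with its 95% CI will be the Aim 3 result. This parallels the existing logistic model for dichotomous measures. State which instruments are scored as continuous. Keep the paired t-tests as a description of change over time, and remove the assumed r = .30 from that sentence.

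The cost is a few lines of analysis text. The baseline scores and race are already collected, and the sample size need not change (159 per arm needed at r = .30, against 176 planned).

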## Methods/design

This prospective, randomized trial involves testing the efficacy of two versions of a printed intervention (i.e., Targeted version and Enhanced Tailored version). Participants will be randomly assigned as family units (YBCS and her high-risk female relatives) to receive one of two versions. The survivor and relative(s) of enrolled family units will be mailed a self-administered baseline survey prior to receiving the intervention (Time 1). A self-administered, follow-up survey will be mailed to YBCS and high-risk relatives nine months post-intervention (Time 2).

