**Behavior**					
Current screening practices	Behavioral risk factors surveillance system [24]	√	√	√	√

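### Change over time in dichotomous outcomes is assigned a chi-square test with no paired form named, although the same women answer both surveys

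*Protocol article*

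**What the plan says.** Under Methods/design, survivors and relatives are surveyed before the intervention, and "A self-administered, follow-up survey will be mailed to YBCS and high-risk relatives nine months post-intervention (Time 2"). Table 2 lists "Current screening practices" at baseline and at follow-up, for survivors and for relatives. Each woman who completes the study therefore gives two linked answers.

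Under Statistical analyses, four statements bear on the point:

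- Descriptive comparisons are made "using the Chi-square test for differences in proportions", alongside an ordinary t-test for means.
- For continuous outcomes: "After assuming an autocorrelation of data r = .30, changes over time in continuous measures will be tested by paired t-tests".
- For dichotomous outcomes with a baseline value, the arms are compared as follows: "logistic regression will be conducted on the post-tests with the pre-tests included as covariates".
- Directly after that: "Chi-square tests will be conducted to test the changes over time".

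**The concern.** An ordinary chi-square test of the Time 1 proportion against the Time 2 proportion assumes two independent samples. Here both proportions come from the same women, and their answers will usually be positively correlated. The test then overstates the variance of the difference, and its p-value is too large.

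The section marks pairing for the t-test and does not mark it here. An analyst following the text would run the unpaired test. At stake is the reported significance of before-after change in screening and genetic counselling use within a group, which the section sets out to assess. The practical risk is that a real rise in screening is reported as not significant.

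**Working it through.** **The plan's own figure.** The Sample size section gives 176 per group, 352 in total and 542 after 35% attrition, for d or h = 0.3, 80% power and two-sided alpha 0.05. The normal formula gives 2 × (1.960 + 0.842)² / 0.3² = 174.4. The two-sample t solution is 175.4, rounded up to 176. Then 352 / 0.65 = 541.5, rounded up to 542. The figure reproduces. It concerns the comparison between arms, so the point here does not touch it.

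**Inputs for the check.**

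- Nominal alpha 0.05 two-sided and power 80%: Sample size section.
- Within-woman correlation ρ: the plan gives r = .30 for continuous measures only. Using it for yes/no answers is an assumption, so a range is shown.

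**Variance.** With n women, a common proportion p and correlation ρ, the change in proportion has variance 2p(1 − p)(1 − ρ)/n. The unpaired chi-square assumes 2p(1 − p)/n. Its 1.96 threshold is therefore a threshold of 1.96k on the correct paired z scale, where k = 1/√(1 − ρ).

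- Real alpha = 2 × [1 − Φ(1.96k)].
- Where a paired test has 80% power, its z has mean 1.960 + 0.842 = 2.802 and SD 1. Power of the unpaired test is then approximately Φ(2.802 − 1.96k).

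| ρ | k | 1.96k | Real alpha | Power where the paired test has 80% |
|---|---|---|---|---|
| .10 | 1.054 | 2.066 | 3.9% | Φ(0.736) = 77% |
| .30 | 1.195 | 2.343 | 1.9% | Φ(0.459) = 68% |
| .50 | 1.414 | 2.772 | 0.6% | Φ(0.030) = 51% |

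Simulation with no true change (176 women, 48% at both times) gave rejection rates of 1.8% at ρ = .30 and 0.5% at ρ = .50 for chi-square, against 4.9% at both for McNemar's test.

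**Illustration at a plausible size.** All of these inputs are assumptions:

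- 357 survivors per arm, from (1,200 − 100) × 0.65 / 2 = 357.5. This takes the expected responders, the estimated exclusions from Aim 3 for hereditary syndromes, and 35% attrition. It pools survivors with and without eligible relatives, whom the plan analyses separately, and it does not apply to relatives.
- 48% at baseline, borrowed from the Background figure for mammography among high-risk Michigan women over 40.
- 56% at follow-up, chosen for illustration.

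At ρ = .30:

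- The unpaired test uses a standard error of √(2 × 0.52 × 0.48 / 357) = 0.0374, so it needs a change of 1.96 × 0.0374 = 0.0733.
- The true standard error is √[(0.2496 + 0.2464 − 2 × 0.3 × 0.248) / 357] = 0.0312. Power is Φ[(0.08 − 0.0733) / 0.0312], about 58%.
- McNemar's test uses the discordant proportions 0.217 and 0.137, a standard error of √(0.354 / 357) = 0.0315 and a threshold of 0.0617. Power is Φ[(0.08 − 0.0617) / 0.0312], about 72%.

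By simulation at ρ = .50 the figures are 59% and 86%.

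**The case against.** The strongest reply is that the wording does not prove an error. McNemar's test has a chi-square reference distribution, and authors who pair their t-tests may well have meant it. The sentence also follows the between-arm regressions, so it could mean a chi-square of change status by arm, which would be valid for independent survivors. And a condensed article may leave the form of a secondary test to the analysis plan.

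Both sound readings are possible, but neither is supported by the text. The section has already used the same term for an ordinary comparison of proportions, it says paired only for the t-tests, and it does not mention a change status. A test is named, and as named it does not fit the data, so this is more than a detail left open.

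The reply is right about scope. Three stronger conclusions that a reader might draw are not supported:

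- **That the trial's main comparison is invalid.** Aim 3 compares two versions of the intervention. For dichotomous outcomes with a baseline this is done by logistic regression adjusted for the pre-test. Both arms are active, so before-after change cannot establish efficacy however it is tested.
- **That false claims of change would follow.** With positive correlation the error is conservative.
- **That the tests would be meaningless.** This would hold if chi-square were run on the Time 1 by Time 2 cross-table, which tests association and not change. With no change, ρ = .30 and 176 women, it would reject in about 98% of trials. Nothing in the text points to that use.

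**Conclusion.** The point holds for the within-group tests of change in dichotomous measures, and only for those. Followed as written, they run at a real alpha of about 1.9% instead of 5%, with about 68% power where a paired test would have 80%, if the plan's r = .30 carries over to binary answers. The loss is small at a correlation of .10 and large at .50. The direction is certain for any positive correlation; the size depends on a correlation that the plan does not give for these outcomes. The sentence should be changed, because before-after change is likely to draw attention if the two active arms do not differ.

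**What to change.** Replace the sentence with one of the following:

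- McNemar's test (exact if discordant pairs are few) with a confidence interval for the paired difference in proportions; or
- a GEE logistic model with a time term, clustered on woman for survivors and on family for relatives, since a family can contribute up to two relatives.

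Keep the logistic regression of the post-test on arm with the pre-test covariate as the Aim 3 test. If McNemar's test was intended all along, naming it settles the matter.

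The cost is one line of analysis text. Both answers per woman are already collected, and neither the sample size nor the surveys change.
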